***Intima-Media Thickness (IMT) and Cerebral Macrovascular (large vessel) Disease***

Carotid IMT is used as an intermediate phenotype for early atherosclerosis, is quantifiable on a linear scale, and is the primary macrovascular outcome variable in this study. Because it can be measured simply and non-invasively, it is well suited to larger clinical studies as an end point to stratify risk. Ultrasonic measurements correlate well with histology (46), and increased IMT is associated with vascular risk factors (7, 8, 49) and the presence of more advanced atherosclerosis (44). ***A systematic review and meta-analysis demonstrated that carotid IMT is a strong predictor of future vascular events (34)***, with an adjusted relative risk of stroke of 1.18 (95% CI, 1.16 to 1.21) per 0.10 mm common carotid artery IMT increase. Our quantification of IMT will follow standardised measurement methodology (55). Ultrasound will be performed by two experienced sonographers under the direction of AI [name], thus minimising between-technician variation.

***The potential for microvascular and macrovascular disease regression with removal of a stimulus has been confirmed in several studies.*** For example, antihypertensive treatment in 25 patients with untreated hypertension over one year was associated with a reduction in retinal arteriolar narrowing, a widening of arteriolar branch angle and an increase in arteriolar density (24). In another study of 51 hypertensive patients, 6 months of antihypertensive treatment was associated with a reduction in mean retinal arteriole diameter of 0.5  $\mu\text{m}$  and a corresponding increase in AVR (47). Thus regression of retinal microvascular disease with effective treatment is a plausible outcome. In addition, there are now several clinical studies that have demonstrated reductions in carotid IMT (indicative of regression of early atherosclerosis) over a six to twelve month period with statin lipid profile altering medications (18, 35, 40). These studies have consistently demonstrated significant regression or slowing of progression of carotid IMT with therapy, and benefits were evident after as little as six to twelve months (40).

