## **PROJECT 2: Regression of Cerebral Vascular Disease in Severe OSAS using CPAP Therapy**

**Hypothesis:** *Early changes of cerebral microvascular disease (indicated by retinal abnormalities) and macrovascular disease (indicated by carotid atherosclerosis and IMT) present in patients with severe OSAS will regress following 12 months treatment with nasal CPAP therapy.*

**Design:** This will be a one-year prospective, longitudinal, observational study of OSAS patients (acting as their own controls). Following discussion with our Ethics Committee, it would not be acceptable to have a randomised, controlled design with a sham treatment arm over a one year period for patients with severe, symptomatic OSAS.

**Subjects:** We will recruit 80 patients from Project 1 (40 in year 1 and 40 in year 2), who have been diagnosed with severe, symptomatic OSAS (RDI >30 events/hr, ESS >9). Exclusion criteria are as for Project 1, plus current smoking or an inability to tolerate CPAP therapy. Successive patients from Project 1 who meet the inclusion criteria will be approached to participate. Over the first two years, our laboratory will diagnose over 400 patients who meet the inclusion criteria.

**Baseline/Anthropometry Data:** Same as for Project 1.

**Procedures:** PSG, Carotid Artery Ultrasound, Retinal Photography as for Project 1.

**Protocol:** Recruited subjects (n=40/year for first 2 years) will complete a run-in period, with review of clinical history, blood lipids, and blood pressure to ensure that subjects have been stabilised on optimal standard therapy for cardiovascular risk factors (normal values with no clinically significant changes). Optimal standard therapy will include continued non-smoking, maintenance of weight, medication (as required) to keep daytime blood pressure and blood lipid profile normal. When clinically stable, diagnostic PSG with repeat carotid Doppler ultrasound (pm) and retinal photography (pm and am) will be performed as a baseline. Subjects will then have a laboratory CPAP titration study, to eliminate snoring and obstructive events as per laboratory protocol.

**The study treatment period will run for 12 months, with monthly monitoring of CPAP compliance** (machine hours at pressure recorded), regular study co-ordinator follow up, and continued monitoring and treatment of cardiovascular risk factors. Subjects will be stratified during analysis according to medication use for cardiovascular risk factors and CPAP compliance.

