**Overnight CPAP review studies using the patient's CPAP treatment pressure will be undertaken at 6 months and one year.** Repeat carotid Doppler ultrasound (pm), retinal photography (pm and am), blood pressure (pm and am), fasting blood lipids and sugar, and weight will be measured.

**This duration of study is adequate to detect clinically relevant outcomes.** An increase in IMT of >0.03 mm/year is detectable and clinically relevant, as it is associated with a doubling in incidence of coronary events (44). We anticipate a reduction of at least this amount (15). For retinal photography, a decrease in 3.5  $\mu$ m/year of arteriolar calibre is detectable, measurable in a one year time frame, and associated with a 10 mmHg increase in mean arterial blood pressure (31), making it clinically relevant. Both arteriolar narrowing and venular widening are predictive of stroke (59).

**We have chosen to compare the same subjects before vs after the intervention but not to have an untreated control arm in this study** due to efficiency of paired comparison and the well recognised ethical problems with not treating severe OSAS. This will enable a valid paired comparison with the differences between the before and after treatment measures being related to the treatment intervention over 1 year. The primary outcome variables (CRAE, CRVE, AVR and IMT) are objective measures of structural changes which are unlikely to spontaneously improve without intervention, or be affected by a placebo type response.

***We acknowledge that compliance with CPAP treatment will be a critical factor to the success of this trial.*** Patients will be offered as much support as required in the initial phases of the trial by the study co-ordinator, with four weekly review throughout the study. Patients will be able to contact the study co-ordinator at any time to resolve problems. CPAP compliance will be monitored objectively by nights and hours of use from machine downloads at study visits, together with compliance with routine medication(s). We will target a minimum compliance of 4 hours per night.

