**Statistical Analysis and Sample Size:** Power analysis is based on data relating to the observed reduction in IMT during CPAP therapy (15). Power calculations show that with a **sample size of 64** we will have 80% power to detect a difference in IMT of 0.025 mm over 12 months, assuming that the common standard deviation is 0.050 mm and using a two group t-test with a 0.05 two-sided significance level. Given the demonstrated reduction in IMT of 9% (0.063 mm) in 24 patients over only four months of CPAP treatment (15), we believe that our power calculation is quite conservative, and that our sample size is robust. Similarly, following 12 months of treatment for hypertension, there have been demonstrated improvements in retinal vessel diameter of 12.5% (24), consistent with the changes in IMT. We will study 80 subjects to allow for a 20% drop-out rate.

**Significance:** A reduction in atherosclerosis (decrease in IMT) and retinal microvascular changes (increase in CRAE, decrease in CRVE) will be related to CPAP therapy, as other cardiovascular risk factors will be stable over the study period, and any other functional changes will be adjusted for during analysis. ***This study will determine if CPAP treatment in patients with severe OSAS results in regression of both cerebral microvascular and macrovascular disease,*** implicating OSAS as a pathogenic factor in cerebral vascular disease, and implying a possible role for treatment of OSAS in risk reduction from cerebral vascular disease.

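### Project 2 credits improvement to CPAP without a control arm, although a blood-pressure or lipid drug effect still developing after baseline could contribute

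*Protocol*

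**What the plan says.** All references are to the Protocol, Project 2, unless stated.

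- **Design.** Patients serve as their own controls. The investigators chose to compare the same subjects before and after treatment "but not to have an untreated control arm in this study", giving efficiency and ethics as reasons.
- **Run-in and baseline (Protocol paragraph).** History, lipids and blood pressure are reviewed "to ensure that subjects have been stabilised on optimal standard therapy for cardiovascular risk factors". Optimal therapy includes "medication (as required) to keep daytime blood pressure and blood lipid profile normal". Then: "When clinically stable, diagnostic PSG with repeat carotid Doppler ultrasound (pm) and retinal photography (pm and am) will be performed as a baseline". Stability means normal values without clinically significant change. No run-in length is given. Monitoring and treatment of risk factors continue through the 12 months of CPAP.
- **Attribution (Significance paragraph).** Improvement in IMT, CRAE and CRVE "will be related to CPAP therapy, as other cardiovascular risk factors will be stable over the study period". The same sentence adds that other functional changes will be adjusted for. The next sentence says the study will determine whether CPAP results in regression.
- **Safeguards.** These are the run-in, the adjustment just mentioned, and stratification at analysis by cardiovascular medication use and by CPAP compliance. The four primary outcomes are also described as "unlikely to spontaneously improve without intervention, or be affected by a placebo type response".
- **Background (section on IMT and large vessel disease).** Statin studies showed "significant regression or slowing of progression of carotid IMT with therapy, and benefits were evident after as little as six to twelve months". One year of antihypertensive treatment was associated with less retinal arteriolar narrowing, and six months with a higher AVR.

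**The concern.** With one group and no concurrent comparator, attributing the change to CPAP requires that nothing else moving IMT or retinal calibre is still acting between baseline and month 12. The plan checks that blood pressure and lipid values are stable. It does not check that the vessel wall has finished responding to the drugs that made them stable. By the protocol's own account that response takes six to twelve months, which is the follow-up window.

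A patient whose values become normal soon after a drug is started or stepped up could pass the run-in while IMT is still falling. That fall would enter the before/after difference and be read as CPAP-induced regression. For IMT and arteriolar narrowing the bias runs in the direction of the hypothesis, and it affects Project 2's central conclusion.

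**Working it through.** **1. The plan's own figure.** The Statistical Analysis and Sample Size paragraph gives 64 evaluable and 80 enrolled for 0.025 mm, SD 0.050 mm, 80% power and two-sided 0.05. A two-group t-test at standardised difference 0.025/0.050 = 0.5 needs 63.8, so 64 per group (power 0.801), and 64/0.8 = 80. The figure reproduces as a per-group number, whereas the study has one group measured twice. That is a separate matter; here it means that the SD of the within-patient change is not stated. I therefore use two values: 0.050 mm (within-person correlation 0.5) and 0.050 × √2 = 0.0707 mm (correlation 0).

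**2. Does the background cover the endpoints that are credited to CPAP?**

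| Endpoint | Drug effect cited in the protocol |
|---|---|
| IMT | Statins: regression or slower progression, evident by 6-12 months |
| Arterioles (CRAE) | One year of treatment: less narrowing (25 patients, previously untreated). Six months: a 0.5 µm fall in mean diameter, opposite to the hypothesised rise |
| AVR | Six months: increase |
| CRVE | None |

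The sample-size paragraph also cites a 12.5% improvement in retinal vessel diameter after 12 months of hypertension treatment.

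**3. Possible shift in mean IMT with no CPAP effect.** Shift = share of patients with a residual drug effect × mean effect still to come after baseline. The documents give neither input. I assume a share of 10-50% and an effect of 0.02-0.03 mm.

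- Low: 0.10 × 0.02 = 0.002 mm; 0.002/0.025 = 8% of the target.
- High: 0.50 × 0.03 = 0.015 mm; 0.015/0.025 = 60% of the target.

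**4. Chance that such a shift is declared significant.** Paired t-test, 64 patients, two-sided 0.05, true CPAP effect zero. With no shift the chance would be 0.05.

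| Drug-only fall in IMT | SD of change 0.050 mm | SD of change 0.0707 mm |
|---|---|---|
| 0.002 mm | 0.06 | 0.06 |
| 0.010 mm | 0.35 | 0.20 |
| 0.015 mm | 0.66 | 0.39 |

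**5. Retina, for scale only.** The pilot mean evening arteriolar diameter was 153.9 µm (Preliminary Data). 12.5% of that is 19.2 µm, against the 3.5 µm per year that the protocol calls clinically relevant. If that full effect arose after baseline in 3.5/19.2 = 18% of patients, the mean would move by 3.5 µm. This is generous to the concern: the cited one-year study treated previously untreated hypertension, whereas here blood pressure is already normal at baseline.

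**6. Do the safeguards close the gap?**

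- *Adjustment for functional changes.* If blood pressure and lipids are normal and stable at every visit, these covariates do not change, so a delayed structural response leaves nothing to adjust for.
- *Stratification by medication use.* Every stratum receives CPAP, so no stratum has an untreated comparator. Use is not defined by time since start or change. An unmedicated stratum would be free of the problem, but its size is unknown.
- *No spontaneous improvement.* The statement concerns change without intervention, and the drugs are an intervention.

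**The case against.** The case against is substantial. The run-in is placed before baseline precisely so that optimisation is complete. The text describes a review to ensure stability and does not say that any patient starts a drug. Adjustment and stratification are both stated, and finer stratum definitions may belong in an analysis plan that is not shown. CPAP compliance, also a stratifier, gives an imperfect dose-response check. Duration of hypertension and current treatment are already recorded. The study is openly labelled observational, and the absence of a control arm is justified on ethical grounds.

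Much of this stands. It means that the bias may be small and that its size cannot be read from the documents. It does not support unqualified causal wording, because the run-in length is unstated and the stability criterion concerns risk-factor values only.

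Stronger readings are tempting but not supported:

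- *That drugs would produce all the credited changes.* No CRVE effect is cited, one study reports a fall in arteriole diameter, and the statin results include mere slowing of progression.
- *That attribution rests on stability alone.* Adjustment is also promised.
- *That drugs probably account for most of the target effect.* The 60% figure needs half the patients to be affected. At 10-20% the shift is 0.002-0.006 mm, or 8-24% of the target.
- *That patients with drug changes should be removed from the primary analysis.* Excluding changes made during follow-up conditions on a post-treatment event: patients who worsen and need more drugs would drop out, which could favour the hypothesis. Power would also suffer. If half were excluded, 32 pairs give power 0.78 for 0.025 mm at an SD of change of 0.050 mm, and 0.49 at 0.0707 mm, where about 65 pairs are needed.

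**Conclusion.** The point holds in a limited form. The protocol states as certain an attribution to CPAP that an uncontrolled before/after comparison cannot establish, while its own background names a concurrent treatment able to move IMT, arteriolar narrowing and AVR over the same period. The stated safeguards reduce the risk without removing it.

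The size is unknown. Under the assumed ranges the shift in mean IMT is 0.002-0.015 mm, or 8-60% of the 0.025 mm target. At the lower end it is negligible. At the upper end a significant result would occur with probability 0.39-0.66 without any CPAP effect, depending on the SD of change. The documents do not show that a drug effect will be present, only that the design could not tell it from a CPAP effect.

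**What to change.** 1. Record the start date and last-change date of each blood-pressure and lipid drug. This has to be captured prospectively, since it may not be recoverable later.
2. Keep all patients in the primary before/after analysis.
3. Define the medication stratum by whether any such drug was started or changed in the 12 months before baseline, and pre-specify a sensitivity analysis in patients with no such change.
4. Report drug changes during follow-up descriptively or in a further sensitivity analysis, never as an exclusion from the primary set.
5. In the Significance paragraph, replace the attribution to CPAP and the claim that the study will determine whether CPAP results in regression. Suggested wording: change associated with 12 months of CPAP on top of optimised risk-factor therapy, with a statement that a drug contribution cannot be excluded without a control arm.

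The cost is a little more data capture, a sensitivity analysis with limited power that remains uncontrolled, and a weaker stated conclusion. No change to patient care is proposed.

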#### **FUTURE DIRECTIONS: Long-term risk of stroke in Heavy Snoring and OSAS Population**

**Hypothesis:** *Long-term lifetime follow-up of a cohort of well-described patients with heavy snoring and OSAS will confirm the excess risk of stroke, and the predominant stroke subtypes.*

We intend to follow patients recruited in this project over their lifetime. Consent for lifetime follow-up for mortality of the subjects recruited in these projects will allow us to determine the risk of stroke. We will obtain date and cause of death via data linkage with the Australian National Death Index, and also obtain subsequent stroke events from the Centre for Health Record Linkage (CHeReL), ***which will not require additional NHMRC funding.*** Our current national follow-up for participants in RCTs (12) allows a cost-effective system of collecting events. This type of follow-up is inexpensive and can be sustained over time by CIA/CIB. There would be a pre-specified plan to continue follow-up at regular future intervals.

#### **OUTCOMES AND SIGNIFICANCE:**

These two projects investigate the macrovascular and microvascular mechanisms of the associations between both heavy snoring and OSAS with an increased risk of stroke. The use of retinal photography (for microvascular disease) and carotid ultrasound IMT (for macrovascular disease) are exciting new investigations which may provide practical clinical tools for stratification of overall cardiovascular risk in snoring and OSAS subjects. In addition, the second study will provide evidence supporting the benefit of CPAP treatment in reduction of cerebral microvascular and macrovascular disease, with consequent stroke risk reduction. Given the high prevalence of snoring and OSAS in the increasingly obese middle to older aged population, findings from these studies will demonstrate a new target for interventions to lower cardiovascular disease risk profiles in the population, and to further reduce the disease burden and premature deaths from stroke and other cardiovascular events.

**[name]** is an ophthalmologist and Director of the Centre for Vision Research, Westmead Millennium Institute, University of Sydney and leads a research program focused on the use of retinal imaging to predict risk of cardiovascular diseases, such as stroke and coronary heart disease. He will work closely with all the CIs in study design, particularly in the area of retinal vascular imaging, and in the analysis of the data, and interpretation of results. As Director of the Department of Ophthalmology, he will take responsibility for diagnosis of any pathological findings on the retinal photographs, that need referral.

**[name]** is an ophthalmologist and currently Professor at the Centre for Eye Research Australia, University of Melbourne and leads a research programme focused on the use of retinal imaging to predict risk of cardiovascular diseases, such as stroke and coronary heart disease. He will work closely with all the CIs in design of the study, particularly in the area of retinal vascular imaging, and in the analysis of the data, interpretation of results, and as a co-author in manuscripts.

**ID:** 570789. **Title:** The Role of Snoring Vibrations in the Pathogenesis of Early Carotid Artery Atherosclerosis. **Chief Investigators:** [name], [name], [name]

This project addresses the hypothesis that snoring induces a series of vibratory pressure waves in the tissue surrounding the pharyngeal airway, that are then transmitted to the carotid artery walls, leading to the development of carotid atherosclerosis through pathogenic effects on the carotid artery endothelium such as endothelial dysfunction. At the end of the second year of funding, all animal studies have been completed, and human studies are in the final stages of data collection. Six abstracts of work completed have been presented, and two manuscripts completed with one publication in 2010 and the second accepted for 2011. Studies undertaken during 2009-2010:

**Project 1a: Natural snoring and carotid artery blood flow in heavy snorers**

Preliminary studies have been completed in three snorers demonstrating that the technique is feasible, and relevant data can be gathered.

**Project 1b: Simulated snoring and human carotid artery blood flow dynamics**

This project uses carotid artery ultrasound to measure blood flow and an oesophageal balloon to monitor pleural pressure during simulated snoring and inspiratory resistive loading at different target levels. Studies have now been completed in six healthy subjects. Loud snores reduce carotid blood flow and wall shear stress. Further normal controls and heavy snorers will be recruited.

**Project 1c: Snoring vibrations and local carotid artery blood flow responses:**

In 10 anaesthetised rabbits, induced snoring and directly applied snoring-like vibrations were studied to assess their impact on carotid artery blood flow and vessel wall shear stress. Induced snoring reduced blood flow and wall shear stress. The direct application of vibrations did not result in any change in carotid artery bulk flow or diameter during vibration.

**Project 2a: Snoring-like vibration of the carotid artery wall causes arterial endothelial injury**

Studies have been completed in 10 anaesthetised rabbits. See Publication number 1.

**Project 2b: Snoring-like vibration of the carotid artery wall causes endothelial dysfunction**

Studies have been completed in 27 anaesthetised rabbits. See publication number 1. These data confirm the hypothesis that snoring vibrations can lead to endothelial dysfunction.

**Aims:** The aim of this study is to further explore the linkage between mild SDB with heavy snoring and early carotid artery atherosclerosis, by demonstrating regression of early changes of carotid atherosclerosis in heavy snorers with mild non-hypoxic SDB, when snoring and SDB are prevented by the use of nasal continuous positive airway pressure (CPAP). The study will achieve this aim by testing for carotid atherosclerosis regression and/or stabilisation (using measures of carotid artery intima-media thickness) with a prospective, randomised controlled study of nasal CPAP in heavy snorers with mild to moderate SDB.

**Hypothesis:** Early changes of carotid artery atherosclerosis seen in patients with heavy snoring and mild SDB will stabilise or regress following treatment with nasal CPAP therapy.

